## Abstract

**Background:**

Relapses and rehospitalisations are common after acute inpatient treatment in depressive disorders. Interventions for stabilising treatment outcomes are urgently needed. Psychoeducational group interventions for relatives were shown to be suitable for improving the course of disease in schizophrenia and bipolar disorders. A small Japanese monocentre randomised controlled trial also showed promising results for depressive disorders. However, the evidence regarding psychoeducation for relatives of patients with depressive disorders is unclear.

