Symptom self-rating (PHQ-9, Core set)		x			x	x	x	x
Rehospitalisations (FIMA, CSSRI-D)					x	x	x	x
Health care and medication consumption (FIMA, CSSRI-D)					x	x	x	x
Employment status^a^		x			x	x	x	x
Days of incapacity to work (DEGS)					x	x	x	x
Functional capability, activity and participation (WHODAS 2.0)		x			x	x	x	x
General state of health (DEGS)		x			x	x	x	x
Perceived expressed emotion (FEF)		x				x		x
Perceived criticism (PCS)		x				x		x
Adverse events^a/IG^						x		x
Clinical characteristics^a^		x						
Demographic information^a^		x						
Relative-related								
Psychosocial burden (SCL-K-9)		x			x	x	x	x
Disease-related burden (IEQ-EU)		x			x	x	x	x
General state of health (DEGS)		x			x	x	x	x
Problem-solving competency (SPSI-R-S)		x				x		x
Implementation of problem-solving^a^						x	x	x
Depression literacy (D-Lit)^a^		x				x		
Control attributions (IPQS-R)		x				x		x
Expressed emotion (FQ)		x				x		x
Health care utilisation (FIMA)		x			x	x	x	x
Employment status^a^		x			x	x	x	x
Acceptance and subjective benefit of the intervention^a/IG^						x		
Adverse Events^a/IG^						x		x
Demographic information^a^		x						

-T_1_, during inpatient treatment; T_0_, at discharge from inpatient treatment; T_A_, allocation to intervention or control group; T_Int_, intervention; Follow-up: T_1_ = 3 months; T_2_ = 6 months; T_3_ = 9 months; T_4_ = 12 months after discharge from inpatient treatment; CSSRI-D, German version of the Client Sociodemographic and Service Receipt Inventory; DEGS, German Health Interview and Examination Survey for Adults; D-Lit, Depression Literacy Test; FEF, Questionnaire on Family Atmosphere; FIMA, Questionnaire for Health-Related Resource Use; FQ, German version of the Family Questionnaire; IEQ-EU, German Version of the Involvement Evaluation Questionnaire; IPQS-R, scales for control attributions of the Illness Perception Questionnaire for Schizophrenia: Relatives’ version; PCS, Perceived Criticism Scale; PHQ-9, 9-item version of the Patient Health Questionnaire; SCL-K-9, 9-item version of the Symptom-Ckecklist-90-R; SPSI-R-S, 25-item version of the Social Problem-Solving Inventory-Revised; WHODAS 2.0, 36-item version of the WHO Disability Assessment Schedule; ^a^self-constructed items; ^IG^only administered in the intervention group

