#### Patient level

Rehospitalisations within the first year after discharge from inpatient treatment, including time until rehospitalisation, will be considered as a secondary outcome (measurement based on the FIMA [44] and the CSSRI-D [45]; time points T_1_ – T_4_). Furthermore, health care utilisation and medication consumption will be assessed (measurement based on the FIMA [44] and the CSSRI-D [45]; time points T_1_ – T_4_). Additionally, employment status (self-constructed items; time points T_0_ – T_4_) and days of incapacity to work (measurement based on the DEGS [46]; time points T_1_ – T_4_) will be measured as secondary outcomes. Rehospitalisation and incapacity to work are relevant outcomes as they are objective indicators of the course of disease. As these outcomes – as well as health care utilisation and medication consumption – are also associated with costs, they are also important from a health economic point of view. As psychoeducation for relatives was shown to be effective for patients’ employment rate for other severe mental disorders [6], and evidence in depression is so far lacking, this was chosen as a secondary outcome. Depressive disorders can lead to impairment of functional capability, activity and participation [47] and affects the general state of health [48]. Therefore, these are relevant outcomes to judge the effect of the intervention beyond the course of disease (measured by the WHODAS 2.0 [49] and a global item regarding the general state of health according to the DEGS [46]; time points T_0_ – T_4_). As expressed emotion is a powerful predictor of relapses in depressive disorders [16], and the intervention is likely to modify the level of expressed emotion, perceived expressed emotion (measured by the FEF [50, 51]; time points T_0_, T_2_, T_4_) as well as perceived criticism (measured by the PCS [51, 52]; time points T_0_, T_2_, T_4_) are interesting intermediate outcomes to understand how the intervention works. In line with the requirement to report potential harm in patients [53], adverse events following the intervention will be assessed in the intervention group (self-constructed items; time points: T_2_, T_4_).

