#### Relative level

Relatives of patients with depressive disorders experience psychosocial burden [54–56]. Therefore, psychological distress (measured by the SCL-K-9 [57]; time points T_0_ – T_4_) and disease-related burden (measured by the IEQ-EU [58, 59]; time points T_0_ – T_4_) were chosen as outcomes to evaluate the effect of the intervention on the relative level. As caregiver burden can affect the health status of relatives [60], the general health status was chosen as an additional outcome to judge the effect of the intervention (measured by a global item regarding the general state of health according to the DEGS [46]; time points: T_0_ – T_4_). As problem-solving competency is considered as a key competency for a healthy family atmosphere [61], this is considered as a secondary outcome (measured by the SPSI-R-S [62, 63]; time points T_0_, T_2_, T_4_). In this regard, the relatives’ implementation of the problem-solving technique conveyed during the intervention is seen as a mediator of the effects (self-constructed items; time points T_2_, T_3_, T_4_). To capture further proximal effects of the intervention, depression literacy will be assessed (measured by the D-Lit [64] and self-constructed items; time points T_0_, T_2_). In addition, control attributions will be examined (measured by scales on control attributions from the IPQS-R [65, 66]; time points T_0_, T_2_, T_4_), as these can be important factors for the development of expressed emotion [65]. Furthermore, expressed emotion will be assessed as an intermediate outcome (measured by the FQ [67]; time points T_0_, T_2_, T_4_). As burden on relatives can also be changed by using various health care services, health care utilisation will be assessed (measurement based on the FIMA [44]; time points T_0_ – T_4_). As caring for a mentally ill person might have an impact on employment activity, employment status will be assessed (self-constructed items; time points T_0_ – T_4_). To judge the intervention from the relatives’ point of view, acceptance and the subjective benefit of the PGIR will be secondary outcomes (self-constructed items; time points T_2_). Following current recommendations [53] and research suggesting potential negative experiences of participants in group settings [68], adverse events will be assessed in the intervention group (self-constructed items; time points T_2_, T_4_).

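### Adverse-event items go only to the intervention group, so events recorded only by them have no control rate

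*Protocol article*

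**What the plan says.** All references are to the protocol article.

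- **Secondary outcomes, Patient level:** "adverse events following the intervention will be assessed in the intervention group", by self-constructed items at T2 and T4. The reason given is "In line with the requirement to report potential harm in patients".
- **Secondary outcomes, Relative level:** "adverse events will be assessed in the intervention group", again by self-constructed items at T2 and T4. Part of the reason is "research suggesting potential negative experiences of participants in group settings".
- **Table 1 (Administration):** the adverse-event rows for patients and for relatives both carry the IG marker, which the footnote explains as "only administered in the intervention group".
- **Abstract, Background:** "Relapses and rehospitalisations are common after acute inpatient treatment in depressive disorders".
- **Administration:** both arms receive postal follow-up questionnaires from the leading centre at three, six, nine and twelve months.

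The wording of the adverse-event items is not shown.

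**The concern.** The items are there to report harm. To say that an intervention caused harm, one needs to know how often the same event occurs without it. This trial has a randomised control group that could supply that rate, and it already writes to that group at the two time points concerned. Under the plan, the controls are not asked.

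The loss falls on any event that the adverse-event items would pick up and no other instrument would. A suicidal crisis that does not lead to readmission is a possible example. For such an event the final report could give only a count in the intervention group. A reader could not tell whether that count is higher than, equal to or lower than what these patients and relatives would have experienced under treatment as usual.

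**Working it through.** **1. Is there a figure to reproduce?** The plan states no adverse-event rate, threshold or precision. The only figures used below are the sample sizes. They reproduce: d = 0.50, 80% power and 5% two-sided (sidedness is not stated, so two-sided is assumed) give 63.77, hence 64 per arm and 128 in total. For the number randomised, 128/0.7 = 182.9 and 128/(0.9 × 0.8) = 177.8, against 180 stated. The point does not depend on either figure.

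**2. What is measured in which arm (Table 1)?**

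| Kind of harm | Two-arm measure (no IG marker) | One-arm only |
|---|---|---|
| Patient: symptom worsening | PHQ-9, T0–T4 | |
| Patient: readmission | Rehospitalisation, T1–T4 | |
| Patient: functioning, health, work | WHODAS 2.0 and general health, T0–T4; days of incapacity, T1–T4 | |
| Conflict in the dyad | FEF, PCS and FQ at T0, T2, T4 | |
| Relative: distress, burden | SCL-K-9 and IEQ-EU, T0–T4 | |
| Any other event | none | Adverse-event items, T2 and T4 |

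The events that the article itself calls common after discharge are relapse and rehospitalisation. Rehospitalisation is compared between arms by Cox regression (Statistical methods, Analyses), and depressive symptoms over the year form the primary outcome. For these, harm can be separated from background. Only the last row lacks a comparator.

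**3. What does a one-arm count show?** Let p1 be the event rate in the intervention group and p0 the rate in controls. Harm is p1 − p0. The plan yields an estimate of p1 and none of p0, so the difference cannot be estimated from these items at any sample size.

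For scale, assume a background p0 of 5% to 50% and no harm at all. With 180/2 = 90 intervention patients, the expected number reporting an event is 90 × 0.05 = 4.5 to 90 × 0.50 = 45.

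**4. What would a second arm buy?** Under the same assumption, the 95% half-width of the difference is 1.96 × √(2p(1 − p)/n) with n per arm:

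- n = 90: 1.96 × √(2 × 0.05 × 0.95/90) = 0.064; 1.96 × √(2 × 0.5 × 0.5/90) = 0.146.
- n = 64 (128/2, the planned analysable number): 0.076 and 0.173.

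The increase detectable with 80% power comes from a two-sided 5% test of two proportions (normal approximation):

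- n = 90: from 5% to about 18%, or from 50% to about 70%.
- n = 64: from 5% to about 22%, or from 50% to about 74%.

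Asking both arms would therefore bound large harms, not rare ones.

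**5. Is it still changeable?** By the Trial status section, enrolment began in March 2015 and data collection runs to March 2017. A patient discharged in March 2015 reaches T2 in September 2015 and T4 in March 2016. At publication in October 2015, every T4 mailing and most T2 mailings were still to come.

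**The case against.** The strongest reply is that most plausible harms are already covered in both arms: deterioration by PHQ-9 and WHODAS 2.0, conflict by FEF, PCS and FQ, burden by IEQ-EU and SCL-K-9, and readmission directly. This stands. A reader might infer from the one-arm items that the trial cannot detect harm of the PGIR at all, or that controls have no comparable assessment. Table 1 contradicts both readings.

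A second reply is that the items may concern the group sessions, which have no counterpart in controls. For relatives this stands in part, because their rationale mentions group settings, and such items belong in one arm. For patients it is weaker. They do not attend the sessions (Intervention and control group), and their rationale is harm reporting. Their items must ask either about events that controls can also have or about what patients themselves attribute to the PGIR. Patients are not blinded, so their attribution cannot replace a control rate. Since the wording is not shown, the share of generic items is unknown, and it cannot be claimed that the count would be mostly background.

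Third, the article promises to report harm, not to compare adverse events, and it treats every analysis beyond the primary one as exploratory. That is true, and descriptive reporting remains possible. It does not make the count interpretable as harm.

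A reader might also infer that extra items in one arm will cause unequal response to the PHQ-9 in the same mailing. The documents do not support this. The Discussion worries about the total number of instruments, not about a difference between arms, and the length of the adverse-event items is not given.

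**Conclusion.** The point holds in a limited form. Events recorded only by the adverse-event items have no comparator, for patients and for relatives, and for those events harm cannot be told from background. This follows from the text and Table 1 without any assumption. How many events it affects is unknown, because neither the item wording nor any background rate is given; the counts and half-widths above rest on an assumed 5% to 50%.

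The primary analysis is untouched, and the two-arm outcomes can still show worsening. What is missing for them is a statement that they will be used to judge harm: the article presents them as measures of effect, mechanism or cost and names only the one-arm items for harm. This is an inexpensive improvement to what the trial can conclude about harm, not a flaw in its main result.

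**What to change.** 1. Split the adverse-event items into those about the group sessions and all others. Keep the session items in the intervention group and label them descriptive.
2. Give the others to both arms at the remaining T2 and T4 mailings, in neutral wording that does not mention the intervention and with the same recall period in each arm.
3. State that comparative harm will be assessed between arms on these shared items and on existing data: PHQ-9 worsening, rehospitalisation, and SCL-K-9 and IEQ-EU worsening in relatives. Report differences with 95% confidence intervals, as exploratory. For the shared items, compare only tandems who were sent the same version.

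Cost: a small amendment and slightly longer control questionnaires. Controls already past T2 will have no T2 data on the shared items. If the amendment is no longer possible, step 3 can still be applied to the existing two-arm outcomes, with all adverse-event items declared descriptive.

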#### Relative level

Relatives of patients with depressive disorders experience psychosocial burden [54–56]. Therefore, psychological distress (measured by the SCL-K-9 [57]; time points T_0_ – T_4_) and disease-related burden (measured by the IEQ-EU [58, 59]; time points T_0_ – T_4_) were chosen as outcomes to evaluate the effect of the intervention on the relative level. As caregiver burden can affect the health status of relatives [60], the general health status was chosen as an additional outcome to judge the effect of the intervention (measured by a global item regarding the general state of health according to the DEGS [46]; time points: T_0_ – T_4_). As problem-solving competency is considered as a key competency for a healthy family atmosphere [61], this is considered as a secondary outcome (measured by the SPSI-R-S [62, 63]; time points T_0_, T_2_, T_4_). In this regard, the relatives’ implementation of the problem-solving technique conveyed during the intervention is seen as a mediator of the effects (self-constructed items; time points T_2_, T_3_, T_4_). To capture further proximal effects of the intervention, depression literacy will be assessed (measured by the D-Lit [64] and self-constructed items; time points T_0_, T_2_). In addition, control attributions will be examined (measured by scales on control attributions from the IPQS-R [65, 66]; time points T_0_, T_2_, T_4_), as these can be important factors for the development of expressed emotion [65]. Furthermore, expressed emotion will be assessed as an intermediate outcome (measured by the FQ [67]; time points T_0_, T_2_, T_4_). As burden on relatives can also be changed by using various health care services, health care utilisation will be assessed (measurement based on the FIMA [44]; time points T_0_ – T_4_). As caring for a mentally ill person might have an impact on employment activity, employment status will be assessed (self-constructed items; time points T_0_ – T_4_). To judge the intervention from the relatives’ point of view, acceptance and the subjective benefit of the PGIR will be secondary outcomes (self-constructed items; time points T_2_). Following current recommendations [53] and research suggesting potential negative experiences of participants in group settings [68], adverse events will be assessed in the intervention group (self-constructed items; time points T_2_, T_4_).

#### Additional parameters

Data on the following demographic parameters will be collected via self-report questionnaire in patients and relatives: age, sex, mother tongue, education, relationship and shared household with the relative, household size, health insurance status (self-constructed items; time point T_0_). On the patient level, data on clinical characteristics will be gathered regarding: medication, previous depressive episodes and previous inpatient treatment, duration of the current depressive episode, first onset of the depressive disorder and self-rated quality of the current inpatient treatment (self-constructed items; time point T_0_).

#### Health economics

A cost-effectiveness analysis (CEA) will be undertaken from the perspective of the statutory health insurance and the society as a whole. A CEA expresses costs in monetary units and outcomes in non-monetary units. Units used for outcomes will be: (1.) DFDs, (2.) prevented sick leave days, and (3.) prevented rehospitalisations. Costs of TAU and of the intervention will be considered according to German guidelines on health economic evaluation [69]. We will consider both direct medical costs and indirect costs due to loss of productivity. Standardised and validated questionnaires (c.f. Table 1) will be used to obtain data about consumption of health resources [44], which will be monetised following current recommendations [70] to illustrate direct medical costs. The incremental cost-effectiveness ratio of the intervention for DFDs, prevented sick leave days and prevented rehospitalisations will be calculated. A budget impact analysis will be conducted along with the economic evaluation to best inform the needs of decision makers regarding affordability and cost-effectiveness of the intervention.

### Measures taken to minimise/avoid bias

#### Randomisation and concealment of allocation

To control for known and unknown confounders and thus preclude selection bias, randomisation of patient-relative tandems will be conducted by means of a computer-based algorithm. Randomisation lists will adhere to a one-to-one study-group allocation ratio and will be stratified by centres with dynamically adaptable block sizes to prevent predictability and to ensure a balanced proportion of participants in both study conditions. To meet the challenges of a group intervention, randomisation blocks will include blocks with two, four, six, eight and ten patient-relative tandems. In each block size, the proportion of patient-relative tandems which will be allocated to the intervention or the control group is balanced. Once a study centre has recruited at least six patient-relative tandems, randomisation will be conducted with the appropriate block size. If a study centre has recruited two or four more patient-relative tandems before the first group session in the intervention group has taken place, they can be re-randomised and added to the PGIR and the control group. Randomisation lists will be centrally generated by the study statistician, who has no direct contact with clinicians or patient-relative tandems. To ensure allocation concealment, randomisation lists will be inaccessible to staff involved in the recruitment at the respective study centres. After recruitment of at least six patient-relative tandems (conducting the PGIR has to be feasible), study sites will report included patient-relative tandems to the leading study centre, which will report the allocation to the study sites as well as the patient-relative tandems. As the effect of the intervention was not moderated by any investigated variable in the study by Shimazu et al. [17], stratification for clinical characteristics will not be considered. However, central clinical variables (e.g., number of depressive episodes, duration of the current episode) will be gathered and their effects will be investigated in additional sensitivity analyses.

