**Methods/Design:**

The study is conducted as a two-arm multisite randomised controlled trial to evaluate the incremental effect of a brief psychoeducational group intervention for relatives as a maintenance treatment on the course of disease compared to treatment as usual. Primary outcome is the estimated number of depression-free-days in patients within one year after discharge from inpatient treatment. 180 patients diagnosed with unipolar depressive disorders as well as one key relative per patient will be included during inpatient treatment and randomly allocated to the conditions at discharge. In the intervention group, relatives will participate in a brief psychoeducational group intervention following the patient’s discharge. The intervention consists of four group sessions lasting 90 to 120 min each. Every group session contains informational parts as well as structured training in problem-solving. In both study conditions, patients will receive treatment as usual. Patients as well as relatives will be surveyed by means of questionnaires at discharge and three, six, nine and twelve months after discharge. In addition to the primary outcome, several patient-related and relative-related secondary outcomes will be considered and health economics will be investigated.

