### Administration

Patient-relative tandems will be screened for eligibility and recruited by the responsible therapists at the respective study centres during inpatient treatment. Informed consent will be sought from all participating patients and relatives (−T_1_, enrolment, c.f. Table 1). At discharge from inpatient depression treatment, a baseline investigation in patients will be conducted in the respective study centres using questionnaires (T_0_, baseline). At the same time, a baseline investigation in relatives will be centrally provided by the leading study centre using questionnaires sent by post (T_0_, baseline). Subsequent to the baseline investigation, patient-relative tandems will be randomly allocated to the intervention or the control group by the leading study centre (T_A_, allocation). As blinding of patient-relative tandems and therapists is not feasible due to the nature of the intervention, patient-relative tandems as well as therapists will be informed about the allocation by the leading study centre (T_A_, allocation). In the intervention group, the intervention should begin as soon as possible after discharge from inpatient depression treatment (T_Int_, intervention). For each relative participating in the PGIR, the therapist in charge receives an allowance of € 50 per group session. For the follow-up measurements in patients and relatives (T_1_ = 3 months; T_2_ = 6 months; T_3_ = 9 months; T_4_ = 12 months after discharge), postal questionnaires provided by the leading study centre will be used. To ensure a sufficient response rate at each time point, patients as well as relatives will receive an unconditional reimbursement of € 5 sent by post together with each questionnaire. In addition, pre-stamped envelopes will be added for returning the questionnaires, as these measures are associated with a better response rate [35]. If patients and/or relatives do not respond, they will be reminded by post after two weeks and by telephone after four weeks.

**Table 1 Tab1:** Study schedule and measurements used

	Study period							
	Enrolment	Baseline	Allocation	Intervention	Follow-up			
Time point	-T_1_	T_0_	T_A_	T_Int_	T_1_	T_2_	T_3_	T_4_
Enrolment								
Patients and relatives								
Eligibility screening	x							
Informed consent	x							
Allocation			x					
Intervention								
Psychoeducational group intervention				x				
Adherence and competence of therapists^a/IG^				x				
Self-rating								
Patient-related								

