### Statistical methods

#### Analyses

The primary outcome, i.e., estimated DFDs one year after discharge from inpatient depression treatment, will be analysed by means of an analysis of covariance (ANCOVA) (independent variables: intervention, study centre; dependent variable: DFDs; covariate: severity of depressive symptoms at baseline) comparing the number of DFDs one year after discharge from inpatient depression treatment between the intervention and the control group. The primary analysis will be performed according to the intention-to-treat principle including all randomised patients. Multiple imputations will be used to account for missing data. Analyses with an alternative method of dealing with missing data and using available data will only be performed as sensitivity analyses in order to test the robustness of the findings. Secondary interval-scaled outcomes will be tested using t-tests and analyses of covariance (ANCOVA, if baseline measurement of the outcome is available). Dichotomous outcomes will be analysed using Fisher’s exact test, chi-square test (depending on expected cell frequencies), or logistic regression (if covariates are present). To ensure the interpretability of the results, each inferential statistical analysis will be accompanied by descriptive analysis. Differences in time until rehospitalisation will be analysed using Cox regression. For parameters in which the variance cannot be calculated analytically (e.g., cost-effectiveness), bootstrap methods will be used. Longitudinal analyses will be performed using general (interval-scaled outcome) or generalised (binary or ordered categorical outcome) linear mixed models. For the primary confirmatory analysis, a result with a type-I error under 5 % (*p* < .05) will be considered as statistically significant. Every additional analysis is seen as exploratory. Accordingly, a correction of the type-I error inflation will not be applied.

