#### Sample size calculation

The effect of the intervention in the study by Shimazu et al. [17] corresponds to an odds ratio of 0.09 (IG: 8 vs. CG: 50 % relapses), equivalent to a Cohen’s d of 1.33, which can be considered as a very large effect. However, the sample size was comparatively small, consisting of only 57 patient-relative tandems. Furthermore, there are some major differences to our study. First, the intervention in our study will be conducted by different therapists at several study sites. Second, our study is closer to routine conditions. Therefore, our study population will be more heterogeneous than in the study by Shimazu et al. [17]. A sample size of 128 patient-relative tandems one year after discharge (T_4_) is sufficient to detect a moderate effect of Cohen’s d = 0.50 (Cohen’s f = 0.25) with a power of 80 % by analysing the primary outcome via ANCOVA. In the study by Shimazu et al. [17], the dropout rate was about 5 %. As our study will be conducted under routine conditions, we estimate a conservative dropout rate of 10 % (*N* = 18) for the time of the intervention and a further 20 % lost to follow-up (*N* = 32). To reach a sample size of 128 patients under consideration of a total dropout rate of 30 %, a total of 180 patient-relative tandems shall be randomised.

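### Randomisation waits for at least six tandems per centre while depression-free days and the rehospitalisation clock run from discharge, so some pre-randomisation time counts as outcome

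*Protocol article*

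**What the plan says.** Three parts of the Protocol article describe when allocation happens.

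- **Abstract, Methods/Design:** tandems are "included during inpatient treatment and randomly allocated to the conditions at discharge".
- **Administration:** T0 is taken at discharge and allocation comes after it, with no time limit. Then: "In the intervention group, the intervention should begin as soon as possible after discharge from inpatient depression treatment".
- **Randomisation and concealment of allocation:** "Once a study centre has recruited at least six patient-relative tandems, randomisation will be conducted with the appropriate block size". Two or four further tandems may be added until the first group session.

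The outcome clock starts at discharge throughout. Study design and Table 1 set T1 to T4 at 3, 6, 9 and 12 months after discharge. The primary ANCOVA is described under Analyses as "comparing the number of DFDs one year after discharge from inpatient depression treatment between the intervention and the control group". Under Secondary outcomes, Patient level, rehospitalisation and the time to it are counted over the first year after discharge, and Analyses assigns the latter to Cox regression.

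The article does not limit the discharge-to-allocation interval, and it does not say how a readmission before allocation is handled.

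**The concern.** Six patients at one centre are not normally discharged on the same day. Under the batch rule, therefore, allocation at discharge cannot hold for every tandem. A patient discharged before the batch is allocated spends the first part of the one-year window not yet randomised. Days in that stretch cannot respond to allocation, yet they are summed into the confirmatory endpoint. A readmission in that stretch would count as an event in the Cox model.

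What is at stake is sensitivity. Time that cannot differ by arm adds noise and shrinks the difference between arms. The covariate, depression severity at baseline, also ages by the length of the wait.

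**Working it through.** **1. The plan's own figure.** Inputs from Sample size calculation and Analyses: "A sample size of 128 patient-relative tandems one year after discharge" "is sufficient to detect a moderate effect of Cohen’s d = 0.50" "with a power of 80 % by analysing the primary outcome via ANCOVA", with significance defined as "a result with a type-I error under 5" %. Sidedness is not stated; two-sided is assumed. With 64 per arm, the noncentral t distribution gives power 0.801 at d = 0.50. Attrition also fits: 180 × 0.9 × 0.8 = 129.6, or 180 − 18 − 32 = 130. The sample size reproduces.

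**2. Time to fill a batch.** Inputs: 180 tandems (Sample size calculation), 8 centres (Study design), 12 months' enrolment (Recruitment and eligibility screening), batch of six.

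- Accrual per centre: 180 / 8 = 22.5 per year, or 1.875 per month.
- Gap between tandems: 365 / 22.5 = 16.2 days.
- First to sixth recruit: 5 × 16.2 = 81 days.
- Mean wait over the six: (5 + 4 + 3 + 2 + 1 + 0) / 6 = 2.5 gaps; 2.5 × 16.2 = 41 days.

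**3. How much of the wait falls after discharge.** This depends on which statement governs.

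- *Reading A: allocation follows every member's discharge baseline (Administration).* The wait is the spread of discharge dates. With equal lengths of stay this equals the spread of recruitment dates, so the mean is 41 days, and a long stay does not shorten it.
- *Reading B: allocation occurs at the sixth recruitment (Randomisation section).* Inpatient time remaining at recruitment, L, absorbs part of the wait: post-discharge wait = max(0, time to sixth recruit − L). L is not given, so it is varied.

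In step 4, Reading B uses random (Poisson) recruitment at the planned rate.

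**4. Dilution, if the effect exists only after allocation and accrues evenly.** d* = 0.50 × (1 − wait / 365), with power at 128 evaluable:

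| Scenario | Mean wait (days) | Share of year | d* | Power |
|---|---|---|---|---|
| No wait | 0 | 0 | 0.50 | 0.80 |
| B, L = 2 months | 8 | 2% | 0.49 | 0.78 |
| B, L = 1 month | 20 | 5% | 0.47 | 0.76 |
| B, L = 0.5 month | 29 | 8% | 0.46 | 0.73 |
| A, or B with L = 0 | 41 | 11% | 0.44 | 0.70 |

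For the last row, 0.50 × (1 − 40.6 / 365) = 0.444; restoring 80% power at that effect would take about 162 evaluable tandems.

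Accrual matters too. At half the planned rate with L = 0 the mean wait is 81 days and power 0.59. At double the rate with L = 1 month it is about 4 days (0.14 month) and power 0.79.

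**5. A side effect of Reading B.** With L = 1 month, 52% of tandems have some post-discharge wait. The other 48% are allocated while the patient is still in hospital, before T0. That contradicts Administration. Because participants are told their arm, the baseline PHQ-9 could then be answered with knowledge of it.

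**The case against.** **The loss of power may already be priced in.** The planned d = 0.50 is set for the outcome one year after discharge, so on the discharge-anchored measure itself. It is far below the 1.33 derived from the earlier Japanese trial. A reader might infer that the trial is simply underpowered at 70%. The article does not support that, because nothing says 0.50 is an effect before delay. Equally, nothing says it allows for delay: the reasons given are several therapists and sites, routine conditions and a more heterogeneous population. The power figures stand only as conditional ones.

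**The wait may be short.** A reader might infer that every tandem loses weeks to months. Recruitment takes place during the inpatient stay, and the randomisation trigger is recruitment, not discharge. Under Reading B many tandems have no post-discharge wait, and the last-discharged tandem has none under Reading A. This stands, and it is why a range is given.

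**Validity is intact.** A reader might infer bias between arms. Pre-allocation days and readmissions precede randomisation and are balanced in expectation, so neither bias between arms nor type I error inflation follows.

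**Discharge is a defensible origin.** The stated question is the course of illness after inpatient treatment, and time spent forming a group is part of delivering a group intervention. This stands against insisting that the confirmatory DFD window be moved; doing so would change the estimand of a trial already enrolling. It does not answer the conflicting statements on timing or the counting of pre-allocation readmissions as events.

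**Late sessions do not undermine T1.** Four fortnightly sessions span 42 days, so the first tandem of a batch could finish at 81 + 42 = 123 days, after T1. But DFDs are based on all of T0 to T4 and do not need T1 to follow the intervention. Table 1 also first re-measures problem-solving competency, depression literacy and expressed emotion at T2.

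**Conclusion.** The point holds as a matter of alignment and efficiency. The article's statements on when allocation occurs cannot all be true for every tandem, and its outcome clocks include time before randomisation for any tandem discharged before its batch is allocated. The effect is attenuation of the DFD difference and of the rehospitalisation hazard ratio.

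At planned accrual the mean wait is about 8 to 41 days, and power at 128 is about 78% to 70%. This rests on equal centre accrual, batches of exactly six, equal stays, an assumed remaining stay of 0 to 2 months under Reading B, no effect before allocation and even accrual of benefit after it, and d = 0.50 not already allowing for the delay. Slower centres, larger batches or variable stays would lengthen the wait; faster centres would shorten it.

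**What to change.** - **Reconcile the text.** Make the abstract, Administration and Randomisation sections agree on when allocation occurs relative to discharge and to T0.
- **Record the allocation date** for every tandem, so that the discharge-to-allocation interval is known.
- **Cox regression:** start the risk period at randomisation, so that earlier readmissions are not counted as events, and state how a patient who is in hospital on that date enters the risk set.
- **Primary ANCOVA:** keep DFDs from discharge and add the discharge-to-allocation interval as a covariate. It is fixed before allocation, so adjusting for it is safe. It removes variation due to the wait but does not undo the dilution.
- **Sensitivity analysis:** DFDs from allocation to T4, expressed as a share of that window. Without a PHQ-9 at allocation, the starting level would have to be interpolated between T0 and the post-allocation T1, which is a further reason to keep this as a sensitivity analysis.
- **Any extra PHQ-9 for waiting tandems** must be completed before allocation is disclosed. Sent with the allocation letter, it would be an unblinded post-allocation measure and unfit as a covariate.

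The cost is some extra analysis work and a somewhat shorter risk period for tandems that waited. The optional PHQ-9 would add one nine-item mailing.
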